**Unexpected adverse reaction**

An adverse reaction, the nature, severity or outcome of which is not consistent with the summary of product characteristics [DIR 2001/83/EC Art 1(13)]9.

This includes class-related reactions which are mentioned in the summary of product characteristics (SmPC) but which are not specifically described as occurring with this product. For products authorised nationally, the relevant SmPC is that authorised by the competent authority in the Member State to whom the reaction is being reported. For centrally authorised products, the relevant SmPC is the SmPC authorised by the European Commission. During the time period between a CHMP opinion in favour of granting a marketing authorisation and the Commission decision granting the marketing authorisation, the relevant SmPC is the SmPC annexed to the CHMP opinion.

**Serious adverse event or serious adverse reaction**

Any untoward medical occurrence or effect that:

- results in death,
- is life-threatening
- requires hospitalisation or prolongation of existing inpatients’ hospitalisation,
- results in persistent or significant disability or incapacity,
- is a congenital anomaly or birth defect.

Life-threatening in the definition of a serious adverse event or serious adverse reaction refers to an event in which the subject was at risk of death at the time of event; it does not refer to an event which hypothetically might have caused death if it were more severe.

Medical and scientific judgement should be exercised in deciding whether expedited reporting is appropriate in other situations, such as important medical events that may not be immediately life-threatening or result in death or hospitalisation but may jeopardise the patient or may require intervention to prevent one of the other outcomes listed in the definition above. *These should also usually be considered serious.*

Examples of such events are intensive treatment in an emergency room or at home for allergic bronchospasm; blood dyscrasias or convulsions that do not result in hospitalisation; or development of drug dependency or drug abuse.

## Expected adverse drug reactions

All expected adverse drug reactions and all expected serious adverse events are listed below ***otherwise they will be reported as SUSARs***.

There are possible side-effects associated with triiodothyronine that can affect individuals in different ways. Serious side effects are rare and include an allergic reaction, chest pain, shortness of breath and arrhythmias. In the treatment of myxedema, side effects associated with the use of intravenous T3 have included arrhythmias (5% of patients) and tachycardia (3%). Hypotension and myocardial infarction occurred in approximately 1.5% of hypothyroid patients that received T3. Angina and congestive heart failure occurred in approximately fewer than 1% of patients.

Other, less serious side effects consist of:

- insomnia;
- headache;
- leg cramps;
- diarrhea, abdominal cramps
- seizures, tremors, nervousness, or irritability;
- menstrual irregularities.
- phlebitis
- Nausea or vomiting
- fever, sweating, or heat intolerance;
- changes in appetite, or weight loss;
- Hypertension
- Skin flushing
- Hypoglycemia
- Adrenal insufficiency

Sometimes, unexpected adverse drug reactions and unexpected serious adverse events become ‘expected’ during the trial, in which case the protocol should be amended and such events would not need reporting. The Chief Investigator and Data Monitoring Committee, will determine whether any events become ‘expected’ during the course of the trial and apply for approval for a substantial amendment.

## Expected Serious Adverse Events

*Expected serious adverse events in patients with COVID19 infection requiring mechanical ventilation or ECMO are listed below(2, 3, 14):*

- Death
- Sudden cardiac death
- Cardiac Arrest
- Electromechanical dissociation
- Pulmonary Embolism
- Venous Thromboembolism
- Disseminated intravascular coagulation
- Myocarditis
- Left Ventricular mural thrombus and/or embolism
- Congestive heart failure
- Cardiogenic shock and hypotension
- Septic shock
- New myocardial infarction
- Angina
- Stroke
- Renal Failure
- Hepatic Failure
- Stress Ulcers
- Bleeding
- Thrombocytopenia
- Ventricular fibrillation or Sustained ventricular tachycardia
- Rythm disturbances and serious bradycardia that require a pacemaker implantation
- [Paroxysmal supraventricular tachycardia](http://emedicine.medscape.com/article/156670-overview), [atrial flutter](http://emedicine.medscape.com/article/151210-overview), and [atrial fibrillation](http://emedicine.medscape.com/article/151066-overview)

#

# Toxicity – Emergency Procedures

Significant toxicity with acute ingestions of T3 is rare. Serious toxicity is more commonly observed with chronic ingestions of large amounts of T4.

According to the Annual Report of the American Association of Poison Control Centers’ National Poison Data System, in 2008, 13,005 exposures to thyroid hormone preparations were documented; of the total listed, 9,006 were single substance exposures. The breakdown by age for single substance exposures is as follows; 5,026 were associated with children younger than 6 years; 554 were associated with persons aged 6-19 years; and 2,957 were associated with those aged older than 19 years. Overall, 3 major adverse outcomes and no deaths were reported.

**Procedures in case of toxicity**

Place patient on close cardiac monitoring.

Withdraw trial treatment

Episodes of ventricular fibrillation or sustained ventricular tachycardia will be treated with cardioversion.

Peri-operative myocardial infarction and angina will be treated according to Guidelines of European Society of Cardiology

Beta-blockers will be administered to counteract the increase in adrenergic activity and treat serious tachyarrhythmias. Asymptomatic patients should not be treated empirically with beta-blockers. Propranolol is a first choice treatment. Propranolol is noncardioselective beta-blocker, widely available. Controls cardiac and psychomotor manifestations within minutes (dose 0.01-0.1 mg/kg IV, 2-5min; titrate to effect). Esmolol could be used alternatively. Esmolol is a short-acting IV cardioselective beta-adrenergic blocker with no membrane depressant activity. Esmolol is an intravenous agent with half-life of 8 min, which allows for titration to effect and quick discontinuation (dose 50-200 mcg/kg/min IV; titrate to effect).

Symptomatic patients require correction of dehydration and control of hyperthermia.

Antipyretics will be used to treat hyperthermia. Acetaminophen is a first choice agent for fever control; It inhibits action of endogenous pyrogens on heat-regulating centers; reduces fever by a direct action on the hypothalamic heat-regulating centers, which, in turn, increase the dissipation of body heat via sweating and vasodilation (dose 325-650 mg PO q4-6h or 1000 mg tid/qid; not to exceed 4 g/d). Aspirin is contraindicated because it displaces T4 from thyroid-binding globulin (TBG), increasing free T4.

Corticosteroids can be used when adrenal crisis is suspected. Hydrocortisone will be used to treat the potential adrenal insufficiency occurring secondary to the hypermetabolic hyperthyroid state (dose 100 mg IV bolus, followed by continuous infusion of 100 mg 8h for 24-48 h).

### Reporting Duties of the Investigator

The Investigator must report any Serious AE (whether or not thought to be related to the investigational drug) by faxing the CRF-AE recording pages **no later than 24 hours** after knowledge of the event to:

### Reporting Duties of Uni-Pharma

Uni-Pharma shall ensure that all relevant information about any Serious and Unexpected Adverse Events considered at least “Possible related” to triiodothyronine (SUSARs) will be reported to the Competent Authorities and Ethics Committees (following general and local rules and procedures), with these deadlines after the knowledge:

- fatal and life threatening unexpected cases, no later than 7 days;
- other unexpected serious cases, no later than 15 days.

Uni-Pharma shall ensure that all information and supporting documentation that subsequently become available, will be also reported as soon as possible to the Competent Authorities.

Since this study is blinded, the patient’s treatment code should be broken (procedure to be specified) before the reporting to the Competent Authorities and the Ethics Committees.

**13. DATA HANDLING AND MONITORING**

The Investigator assumes the responsibility to assure that the study will be conducted according to the protocol, the Good Clinical Practice (GCP) and ICH guidelines, local laws and obligations and the World Medical Association Declaration of Helsinki (Appendix 1) and that all valid data will be entered into the CRF.

Individual patient medical information obtained as a result of this study is considered confidential and disclosure to third part is prohibited.

The data must be recorded in the CRF, there should be an explanation for missing data, there should be no empty spaces, if a test is not performed, it should be written «NO», or the empty space should be barred. The data should be recorded with a black pen and in a legible way. In case of error, the error should be cancelled with a single line, the correct data should be written beside, and the correction should be dated and signed. If necessary the motivation for the correction should be indicated, data should never be obscured by use of corrective fluid or by overwriting.

The Investigator/s should prepare and store the lists of screened and randomised patients. For each one the following information should be included: identity, complete address, study number of patient, date of screening, date of enrolment and date of randomisation.

The Investigator/Institution will permit the representative of the Sponsor and the CRO to review in detail the CRF and the related data/original documents.

**14. STATISTICAL ISSUES**

Specification on statistical evaluation for efficacy and safety parameters

Continuous variables will be described using descriptive analysis like mean and median value, standard deviation, range, minimum and maximum; categorical variables will be described using relative and absolute frequencies.

Summary values will be expressed as mean ± SD. Categorical data will be compared by using Chi-square and the Fisher’s exact test. Normal distribution of variables will be estimated with Kolmogorov-Smirnov test. Normally distributed data will be compared using an independent t test. Skewed data will be analyzed non-parametrically (Mann-Whitney U or Kruskal-Wallis test). Serial measurements will be compared by repeated measures analysis of variance (RMANOVA). When significant, differences within and between each group will be tested by a post hoc analysis using the Bonferroni correction for multiple comparisons. A computerized statistical program (SPSS for Windows) will be used for all analyses. All tests will be 2-sided. The p values <0.05 will be considered statistically significant.

Survival analysis will be performed using clinical data obtained at follow-up (major and minor events). Kaplan-Meier method will be used to describe the overall survival and the length of the progression-free interval. Log-rank test will be used to compare survival curves. Univariate and multivariate analysis using the Cox regression model will be performed in order to eliminate eventually confounding factors.

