**Assessment of weaning from cardiorespiratory support**

- Successful weaning is defined as no requirement for ventilatory support after extubation (mechanical support) or support from ECMO for 48 hours. The primary objective will be measured as percentage of patients successfully weaned after 30 days of follow-up. The percentage of patients weaned at 20 days post-intubation will be a relevant secondary endpoint.

The ***secondary objectives*** of the study are:

1. **Assessment of hemodynamic status**

Hemodynamic status will be assessed by continuous blood pressure measurements (systolic, diastolic and mean BP) and the use of inotropic and vasoactive drugs.

1. **Assessment of pulmonary function**

Pulmonary function will be assessed by arterial measurement of blood gases, Horowitz-Index (pO2/FiO2) and lactate.

1. **Assessment of hepatic and renal function**

Hepatic and renal function will be assessed by laboratory measurements in blood and urine volume

1. **Assessment of cardiac function**

Echocardiographic assessment of systolic and diastolic function will be performed. Measurements of cardiac troponin-I will be used to assess myocardial injury

1. **Assessment of the course of** *COVID-19* **infection**

COVID-19infection will be assessed by inflammatory indices and their course (daily changes and absolute values) in blood (IL6, Procalcitonin, D-Dimers, Ferritin and CRP), temperature monitoring and time needed for the patient to become negative in COVID-19.

1. **Assessment of clinical outcome and safety**

Major events (*death, cardiac Arrest, electromechanical dissociation, pulmonary embolism, new myocardial infarction, stroke, pulmonary edema, cardiogenic shock and hypotension, septic shock, pulmonary embolism, serious bleeding*) and minor (*myocarditis, Venous Thromboembolism, left Ventricular mural thrombus, renal failure, hepatic failure, stress ulcers, minor bleeding,* [*paroxysmal supraventricular tachycardia*](http://emedicine.medscape.com/article/156670-overview)*and*[*atrial fibrillation*](http://emedicine.medscape.com/article/151066-overview)*, rythm disturbances*) will be recorded during the follow up period.

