## Baseline data

All patients will have a full medical history taken and a clinical examination. The following are to be recorded:

- ***Patient profile*** (Height, Weight, gender, Race, Age and date of birth, Address and phone number, significant past medical history, smoking, time from onset of symptoms to admission)
- ***Any Co-morbidities***
- ***Medication at admission in ICU***
- ***Blood pressure and heart rate***
- ***Blood gases*** (pO2, pCO2, blood pH, lactate)
- ***Echocardiographic analysis***
- ***ECG***
- ***Standard Laboratory data:*** *Haemoglobin, White blood cells, platelets, urea, creatinine, glucose, CPK, LDH, AST, ALT, γ-GT, Total and Direct bilirubin, Albumin and total protein, INR, IL6, Procalcitonin, Ferritin, d-dimer,fibrinogen, electrolytes (Na, K, Ca, phosphate, Mg), troponin I, BNP, CRP, erythrocyte sedimentation rate*
- ***24h urine volume***

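### Skewed secondary markers are compared without a baseline covariate and, when serial, by repeated measures ANOVA on no stated scale; a log-scale, baseline-adjusted analysis gains power if baseline correlation is about 0.5 or more

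*Protocol*

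**What the plan says.** Protocol section 14 sets a chain for continuous variables. First, "Normal distribution of variables will be estimated with Kolmogorov-Smirnov test". Then "Normally distributed data will be compared using an independent t test", and otherwise "Skewed data will be analyzed non-parametrically (Mann-Whitney U or Kruskal-Wallis test"). For repeated values, "Serial measurements will be compared by repeated measures analysis of variance (RMANOVA"). No transformation is named and no baseline covariate appears for continuous outcomes. Covariates are mentioned only for the Cox model.

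The markers at issue are secondary. Section 3 asks for "inflammatory indices and their course (daily changes and absolute values) in blood (IL6, Procalcitonin, D-Dimers, Ferritin and CRP"), and also lists lactate, troponin I and hepatic and renal laboratory values. Section 11, Baseline data, already collects "IL6, Procalcitonin, Ferritin, d-dimer,fibrinogen, electrolytes (Na, K, Ca, phosphate, Mg), troponin I, BNP, CRP, erythrocyte sedimentation rate", and lactate with the blood gases. Section 11, Study assessments, repeats laboratory tests and blood gases every 24 hours in the ICU. Section 6 plans 30 patients per arm with two-sided alpha 0.05.

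**The concern.** Markers of this kind are usually right-skewed, and a patient's later value usually depends on the starting value. In a trial of 60 patients, chance baseline differences and between-patient spread can hide a real effect. Neither the t test nor Mann-Whitney on a follow-up value uses the baseline measurement. Repeated measures ANOVA can include baseline as a time point, but that is less efficient than using it as a covariate. As written, with no transformation named, it would also be run on raw skewed values.

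At stake are the power and readability of the infection-course, tissue-hypoxia and myocardial-injury comparisons. A data-driven choice can also give a mean difference for one marker or day and a rank comparison for the next, so results are not on a common scale.

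**Working it through.** **The plan's own figure.** The protocol gives no power for any marker. Its only power figure is 84% for the primary endpoint (15% against 50%, 30 per arm). With mean proportion 0.325, the null standard error is √(2·0.325·0.675/30) = 0.1209 and the alternative one is √((0.15·0.85 + 0.5·0.5)/30) = 0.1122. Then (0.35 − 1.96·0.1209)/0.1122 = 1.01, which is 84.3%. It reproduces and is not in question here.

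**Assumptions for the markers (not in the protocol).** Log-normal values, equal variances, complete data, 30 per arm, two-sided 0.05. Log SD σ, baseline-to-follow-up correlation r on the log scale, and the true ratio of 2 (log difference 0.693) are assumed.

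**1. Does the pre-test do harm?** The rule was simulated as Kolmogorov-Smirnov in each arm, raw t test if both arms pass, otherwise Mann-Whitney.
- Type I error is 0.048 to 0.056.
- With plain critical values, both arms pass in about 32% of trials at σ = 1.0 and 8% at σ = 1.3.
- With Lilliefors critical values, the raw t test is chosen in about 0.4% of trials at σ = 1.0. The protocol does not say which version applies.
- Power at ratio 2 is about 72% (σ = 1.0) and 50% (σ = 1.3), within about 2 points of Mann-Whitney throughout.

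**2. What does baseline adjustment add for a single time point?** ANCOVA reduces the residual SD to σ√(1 − r²). The non-centrality is 0.693 / (σ√(1 − r²)·√(2/30)), with 57 degrees of freedom. At σ = 1.0 and r = 0.5 this is 0.693/(0.866·0.258) = 3.10, a power of 86%.

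| r | log ANCOVA power, σ = 1.0 | σ = 1.3 | minus stated rule (72%, 50%) |
|---|---|---|---|
| 0 | 75% | 53% | 3, 3 |
| 0.3 | 79% | 57% | 7, 7 |
| 0.5 | 86% | 65% | 14, 15 |
| 0.6 | 91% | 72% | 19, 22 |
| 0.7 | 96% | 81% | 24, 31 |

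The formula ignores chance baseline imbalance, so it runs about a point high. Simulated gains, which vary by a point or two between runs, are about 1 to 2, 6 to 8, 13 to 14, 18 to 21 and 23 to 32 points. At σ = 0.7 the stated rule already has about 95% power, so the gain is under 5 points even at r = 0.6.

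The r = 0 row shows what the log scale gives without baseline information: very little.

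**3. Serial markers.** A second simulation used baseline plus three later values, equal correlation between all time points, a constant effect of 0.515 log-SD after baseline, and r from 0.3 to 0.7. The effect differs from step 2, so the two sets of power are not comparable.

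| σ | raw RMANOVA, group effect | raw RMANOVA, group × time | log ANCOVA of mean post-baseline value |
|---|---|---|---|
| 0.5 | 0.34–0.50 | 0.28–0.57 | 0.83–0.94 |
| 1.0 | 0.25–0.39 | 0.17–0.30 | 0.83–0.94 |
| 1.5 | 0.17–0.27 | 0.07–0.13 | 0.83–0.94 |

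Scale explains part of this. At σ = 1.0 and r = 0.5, moving RMANOVA to the log scale raises the group effect from 0.31 to 0.46 and group × time from 0.19 to 0.49. ANCOVA of the mean post-baseline value reaches 0.85.

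**The case against.** The strongest objection is that this is a conditional preference about secondary outcomes. The protocol gives no correlation. At r = 0.3 or below the single-time-point gain is small, and at 0 it is close to nil. That stands, and it is why the gain is given as a range.

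A statistical analysis plan, not available here, may set scale and covariates. This stands in part: detail may be added there, but the protocol names the tests, and ANCOVA would replace them.

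Section 3 asks for daily changes, which use an earlier value. If change is taken from baseline, this recovers some of the loss. On the log scale with equal variances at r = 0.6, the variance factor is 2(1 − 0.6) = 0.80 for change against 1 − 0.6² = 0.64 for ANCOVA.

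Section 14 states "Summary values will be expressed as mean ± SD", which suits skewed markers poorly, but it also lists the median and range, so little rests on that line.

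A reader might infer that the Kolmogorov-Smirnov step is the main fault, or that raw t tests will often be run on strongly skewed markers. The calculations do not support either. Skewed data mostly go to the rank test, and error rates hold. Nor do all the secondary objectives rest on the t or Mann-Whitney choice, because the daily markers fall under the repeated measures sentence.

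**Conclusion.** The point holds as a minor, low-cost improvement to the secondary analyses. The stated tests leave collected baseline values unused as covariates, and serial skewed markers go to repeated measures ANOVA with no scale stated. For a single time point at ratio 2, 30 per arm and log SD 1.0 to 1.3, the gain from log-scale ANCOVA is worthwhile (13 points or more) at baseline correlation of about 0.5 and above, and small at 0.3 or less. For serial markers the simulated loss is larger, under a constant post-baseline effect and an ANOVA that includes baseline as a time point.

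It would go too far to call the log-scale analysis clearly more powerful without condition, because the protocol supplies neither correlation nor SD. All figures assume complete log-normal data. Death, weaning and ICU discharge before later samples were not modelled. The primary endpoint is not affected.

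**What to change.** Before unblinding, name the skewed markers (at least IL-6, procalcitonin, D-dimer, ferritin, CRP, lactate and troponin I). For these, replace both the t or Mann-Whitney choice and raw-scale repeated measures ANOVA with a pre-specified analysis of the log value, with log baseline as covariate. This can be ANCOVA for a stated time point or for the mean post-baseline value, or a repeated-measures model with baseline as covariate. Report ratios of geometric means with confidence intervals, and describe the markers by median and quartiles. The normality pre-test then has no role for these markers.

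The cost is wording only, since baseline values are already collected. Two additions are needed: a substitution rule for values below the assay limit, and a stated way of handling values missing after death or ICU discharge, which this change does not solve.

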**1. SUMMARY**

**Study title and code:**

Triiodothyronine (T3) for the treatment of critically ill patients with COVID-19 infection ***("ThySupport")***

**EudraCT No:** 2020-001623-13

**Study type and design:** This study is a phase II, parallel, prospective, randomized, double-blind, placebo controlled trial.

**Study aim:** The present study aims to address the efficacy and safety of acute administration of T3 on ICU patients diagnosed with pulmonary infection due to COVID-19 that require mechanical respiratory support or ECMO.

**Study treatment:** Intravenous T3 administration in ICU patients *diagnosed with pulmonary infection due to COVID-19*.

**Number and characteristics of patients:** 60 ICU patients (Age> 18 years old) diagnosed with pulmonary infection due to COVID-19 requiring mechanical respiratory support or ECMO will be included in the study.

**Study duration:** The study will start at June 2020 and is programmed to be completed by June 2021. Treatment period will last till successful weaning or end of follow-up. Follow up will be performed for 1 month.

**Objectives:** The ***primary objective*** of the study is to determine whether the administration of intravenous T3 in ICU patients *diagnosed with pulmonary infection due to COVID-19* facilitates weaning from cardiorespiratory support compared to placebo.

**Main efficacy criteria:** The primary end-point assessed in the present study will be the percentage of patients successfully weaned after 30 days of follow-up after intubation. Successful weaning is expected in 15% of patients at 30 days in placebo group. We assume that T3 treatment can increase successful weaning to 50% of patients which is a significant clinical improvement in prognosis.

**Safety criteria:** The following safety criteria will be assessed: cardiac and non-cardiac death, cardiac arrest, electromechanical dissociation, pulmonary embolism, new myocardial infarction, stroke, pulmonary oedema, cardiogenic shock and hypotension, septic shock, serious bleeding, episodes of arrhythmias (paroxysmal supraventricular tachycardia, atrial fibrillation, sustained ventricular tachycardia). Any iindividual adverse event (AE) will be evaluated by the investigators and they will be reported to the sponsor and Coordinator during the duration of the study.

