**Sponsor statement:**

### The study will be conducted according to this protocol, the Good Clinical Practice (GCP), the ICH guidelines, local laws and obligations and the World Medical Association Declaration of Helsinki *(Appendix 1)*.

**2. BACKGROUND AND RATIONALE**

**Background**

**Introduction**

Covid-19 has caused a pandemic with increased mortality in the population particularly in aging people and patients with chronic disease. A number of infected patients require hospital care and severe cases are admitted to ICU (intensive care units) due to sepsis/septic shock. The mortality rate of patients requiring ICU treatment was reported to be between 81%-97% (1, 2).

Sepsis is a complex disorder that develops as deregulated host response to an infection and is associated with acute organ dysfunction and a high risk of death.

The world health assembly and WHO made sepsis a global health priority in 2017 and have adopted a resolution to improve the prevention , diagnosis and management of sepsis. 2.8 million deaths per year are attributable to sepsis(3).

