## Study assessments

***During stay in the ICU the following parameters will be recorded every 24 hours:*** Blood pressure, heart rate, oxygen saturation, temperature, blood gases, urine volume, need for inotropic support, standard medication, laboratory tests, ECG and evaluation of AEs.

**Echocardiographic analysis** will be performed every 48 hours during ICU stay

**Thyroid hormone levels** (Serum total T3, total T4 and TSH) will be determined at baseline and at 24h, 48h, 72h, and every 3 days till termination of drug administration or end of follow-up.

**Successful weaning** will be defined as no requirement for ventilatory support for 48 hours after extubation, or (in tracheostomised patients) discontinuation of ventilatory support or no need for ECMO support for 48 hours. The percentage of successfully weaned patients and the duration of required mechanical respiratory support or ECMO (in days) will be recorded.

**Individual adverse events** (AE) will be evaluated by the investigators and they will be reported to the sponsor. This includes the evaluation of seriousness, causality and expectedness and any relationship between the investigational medicinal product(s) and/or concomitant therapy and the adverse event. Adverse events will be recorded during 30 days follow-up. A 24h telephone line will be available for all patients in order to communicate with a study investigator and report any adverse event in the case of discharge from hospital.

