## Procedure to account for missing or spurious data

All efforts will be directed towards minimizing the amount of missing data likely to occur. The percentage of missing values for a given variable in this study is expected not to exceed 5%.

Imputation of missing data is going to be performed based upon maximum-likelihood methodology. The maximum-likelihood based strategies fit a model by an iterative process (the Expectation maximisation algorithm). Multiple imputation methods generate multiple copies of the original dataset replacing missing values by randomly generated values and analyse them as complete sets.

Mixed effects models are proposed to be used to impute missing data of repeated measurements over time outcomes. Time of measurement may be considered as a random variable and these models may estimate a slope to summarize each patient’s response.

A sensitivity analysis will be performed at the end of the study in order to justify the choice of the particular method applied for handling missing data. Sensitivity analysis will consist of the following steps:

1. Comparison of the results of two analyses, one assigning the best possible outcome to all missing values in both groups and the other assigning the worst possible outcome to all missing values in both groups
2. Comparison of the results of two analyses, one assigning the best possible outcome to missing values in the control group and the worst possible to those of the experimental group and vice-versa.
3. Comparison of the results of the full set analysis to those of the complete case analysis

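### RMANOVA with imputation and a 5% missing-data expectation for serial ICU measurements does not separate unrecorded values from values that cannot exist after death or ICU discharge

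*Protocol*

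**What the plan says.** Section 14 of the protocol fixes the method for repeated data: "Serial measurements will be compared by repeated measures analysis of variance (RMANOVA"). It names no time window.

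The subsection on missing or spurious data states: "The percentage of missing values for a given variable in this study is expected not to exceed 5" per cent. On the remedy it says: "Mixed effects models are proposed to be used to impute missing data of repeated measurements over time outcomes". It then lists three sensitivity steps: best against worst outcome for all missing values, best and worst crossed between the arms, and full set against complete cases. None of them mentions death.

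Section 11 (Study assessments) schedules the daily vital signs, blood gases and laboratory tests, and echocardiography every 48 hours, during ICU stay. It also says that "the duration of required mechanical respiratory support or ECMO (in days) will be recorded", with no analysis attached.

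For events, section 14 plans a survival analysis of major and minor events and adds: "Kaplan-Meier method will be used to describe the overall survival and the length of the progression-free interval". The progression-free interval is not defined, and no competing-risk method is named.

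Two figures show how common death may be. The Introduction in section 2 reports: "The mortality rate of patients requiring ICU treatment was reported to be between 81%-97" per cent. The Summary states: "Successful weaning is expected in 15% of patients at 30 days in placebo group", with 50% assumed on T3.

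**The concern.** Most secondary objectives in section 3 are serial: haemodynamics, pO2/FiO2 and lactate, hepatic and renal function, echocardiography, and inflammatory markers. In this population many series stop because the patient dies, and others stop because the patient recovers and leaves the ICU. Neither is an ordinary missing value.

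Classical RMANOVA keeps only patients with every time point. The stated remedy is to impute what is absent. The first route compares selected patients. The second can produce blood pressures and blood gases for patients who have died. If T3 changes mortality, the patients still under observation differ in prognosis between the arms, and a marker that T3 does not affect can appear to differ. A similar problem affects non-fatal events if deaths are treated as ordinary censoring.

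**Working it through.** **The plan's own figures.** The 84% power in section 6 reproduces and is not in dispute. With 15% v 50%, 30 per arm and two-sided 0.05, z = (0.35 − 1.96·√(2·0.325·0.675/30)) / √(0.15·0.85/30 + 0.5·0.5/30) = 0.113/0.112 = 1.01, which gives 84.3%. The 5% missing-data figure has no derivation to reproduce.

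**Mortality range.** The protocol states no trial mortality. I assume that a fraction f of unweaned patients die and that nobody dies after weaning. Placebo mortality is then 0.85f and T3 mortality 0.50f.
- f = 0.5: 42.5% and 25%, or 33.75% overall.
- f = 1: 85% and 50%, or 67.5% overall.
- Placebo at 81%, the lower background figure: f = 0.81/0.85 = 0.953, so T3 is 47.6%.

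**Values lost to death.** With a constant hazard (assumption) and 30-day mortality m, the share of an arm dead by day t is 1 − (1 − m)^(t/30).

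| m | day 7 | day 14 | mean over days 1–30 |
|---|---|---|---|
| 25% | 6.5% | 12.6% | 13.5% |
| 42.5% | 12.1% | 22.8% | 23.9% |
| 81% | 32.1% | 53.9% | 52.6% |

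Death alone takes more than 5% by day 7 once m exceeds 1 − 0.95^(30/7) = 20%. ICU discharge removes further values.

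**Selected subset.** At 81% v 47.6% mortality, the patients alive at day 30 number 30·0.19 = 5.7 on placebo and 30·0.524 = 15.7 on T3. These are upper bounds for a complete daily series, because survivors who leave the ICU also drop out.

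**Bias from comparing survivors.** This was an illustrative simulation with 30 per arm. The marker was not affected by T3, the log-odds of death rose by an assumed 1.5 per SD of the marker, and survivors were compared by t test.
- 81% v 47.6% mortality: about 16% false positives, and T3 looks 0.42 SD worse.
- 42.5% v 25%: about 9%, and 0.19 SD worse.
- 81% in both arms (check): 5.3%, with no bias.

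**Non-fatal events.** Suppose deaths are censored and 1 − Kaplan-Meier at day 30 reads 20%. With constant hazards λe = −ln(0.8)/30 and λd = −ln(1 − m)/30, cumulative incidence is λe/(λe + λd)·(1 − e^(−30(λe + λd))).
- m = 42.5%: 15.5%, so 20% overstates it 1.3 times.
- m = 81%: 10.0%, so 20% overstates it 2.0 times.

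**Duration of support, if it were compared raw.** Constant hazards were simulated.
- Same weaning hazard, mortality 81% v 50%: mean duration is 8.9 days on placebo and 15.8 on T3, although support-free days favour T3 (3.3 v 4.9).
- The plan's 15% v 50% weaned, mortality 81% v 47.6%: raw means are 8.9 v 7.8 days and support-free days 3.3 v 11.3. The raw figure is not reversed here, but it hides most of the benefit.

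**The case against.** The strongest reply is that the missing-data text speaks of missing values, while the daily measurements are scheduled only during ICU stay. Values after death or discharge were then never due, 5% refers to scheduled data not collected, and nothing contradicts the mortality figures. That reading is available, so the 5% need not be deleted. It does not rescue the analysis. If post-death values are missing, the 5% is unrealistic and imputation fills them in. If they are not missing, classical RMANOVA drops the patient. The best/worst-case steps do not help either: applied to deaths, the best-case assignment would give patients who died the best possible value.

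Other parts of the reply stand, and they limit the point:

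- A reader might infer that the plan ignores death. It does not. Overall survival has a valid Kaplan-Meier and log-rank analysis, and death is a listed major event.
- A reader might infer that raw duration of support will be compared. The protocol only says that it is recorded; it is not among the secondary objectives in section 3.
- A reader might infer that viral clearance ("time needed for the patient to become negative in COVID-19") will be analysed by Kaplan-Meier with deaths censored. No method is assigned to it.
- Kaplan-Meier is named only for overall survival and the progression-free interval. The latter is sound if death counts as an event. The text neither says so nor says that deaths are censored for other events.
- A reader might take 81–97% as the trial's expected mortality. It is a background range. With 50% weaned on T3, overall mortality is at most 67.5% if nobody dies after weaning. A placebo figure of 97% cannot sit beside 15% weaned (together 112%) unless weaned patients die later.

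**Conclusion.** The point holds for the serial secondary measurements. Section 14 fixes a method, an imputation approach and a missing-data expectation that do not separate unrecorded values from values ended by death or ICU discharge. Death alone removes about 6.5% to 32% of an arm's values by day 7 across 30-day mortality of 25% to 81%, so the conclusion does not depend on the high background figure. These percentages assume a constant hazard. The mortality range below 81% assumes that at least half of unweaned patients die and that none die after weaning. The size of the bias also depends on how strongly a marker predicts death and on mortality differing between arms, and neither is given in the protocol.

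For events, the survival analysis of major and minor events lacks a competing-risk rule, and the progression-free interval is undefined. The documents do not support saying that the plan disregards death, or that it commits to a raw comparison of duration. The weaning endpoints at days 20 and 30 and the overall survival analysis are not affected. This should be corrected, but it does not undermine the primary result.

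**What to change.** In section 14:

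- Replace RMANOVA with a likelihood-based mixed model on observed values, with arm, day, arm-by-day and the collected baseline value as a covariate, over a fixed early horizon such as day 7.
- State that nothing is imputed after death. Restrict the 5% expectation to scheduled measurements in patients alive and in the ICU.
- Add a supportive rank analysis with death as the worst outcome. The mixed model alone does not settle the matter, because it describes patients still under observation and treats the end of a series as ignorable.
- In the survival analysis of major and minor events, use cumulative incidence with death as a competing event for non-fatal events.
- Define the progression-free interval with death as an event, or delete it.
- If duration of support is compared between arms, use support-free days to day 30 with death set to 0.

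The cost is revised wording and slightly more programming, with no change to sample size or data collection. The drawback is that while-alive and rank results are harder to describe than a difference in means.
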